**Table 3 T3:**
[figure not shown]
Quantitative standard for the classification of symptoms and signs.

The criteria for determining the therapeutic effect of TCM will be formulated in accordance with the guiding principles for clinical research for new TCM drugs^[25]^ (Trial) and the criteria for the therapeutic effect of the diagnosis of diseases and syndromes of TCM issued by the Chinese Society of TCM.

(1)Cure: the clinical symptoms and signs disappear or basically disappear, and the laboratory examination reveals visible improvement. The TCM syndrome score is reduced by more than 95%.(2)Significant effect: the clinical symptoms, signs, and laboratory tests are significantly improved. The TCM syndrome score is reduced by ≥70%.(3)Effective: the clinical symptoms, signs, and laboratory tests are improved. The TCM symptom score is reduced by ≥30%.(4)Invalid: the clinical symptoms and signs are not improved or have worsened. There is a < 30% reduction in the TCM symptom score.

2. PɑO2/FiO2: before and after the intervention, we will perform arterial blood gas analyses to measure changes in the PɑO2/FiO2.

3. Extravascular pulmonary water index: will be obtained from the PiCCO monitor (It is a tool to detect the main hemodynamic parameters of severe patients)

4. Length of time with ventilator: the time with the ventilator will be 14 days from the patient participating in the trial to the treatment.

5. ICU length of stay: the actual length of stay = date of leaving the ICU - date of entering the ICU + 1.

6. 28-day mortality: the mortality rate from the beginning of the trial to the 28th day will be recorded.

7. Follow-up records: During the follow-up period, the all-cause mortality, respiratory failure mortality, and readmission rate in the 1-year period after discharge will be recorded. Criteria for readmission: subjects readmitted for ARDS or other respiratory diseases, not including any other disease or reason. If readmission occurs during the follow-up period, the readmission rate will not be recorded during the follow-up period. Readmission rate = number of patients readmitted/number of patients who completed follow-up.

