## Introduction

1

Acute respiratory distress syndrome (ARDS) is a common clinical disease characterized by acute hypoxemia, decreased lung compliance, and non-cardiogenic pulmonary edema, which can cause a series of serious complications and even progress to multiple organ failure.^[1–4]^ ARDS can be attributed to a variety of factors, including sepsis, multiple injuries, massive blood transfusions, pneumonia, aspiration, and lung contusions, among others. The primary pathophysiological feature of ARDS is the accumulation of a large amount of protein-rich fluid in the alveolar space due to damage of the diffuse alveolar capillary barrier.^[5–7]^ Although comprehensive studies have provided clinicians with a better understanding of the complex pathogenesis of ARDS, the incidence rate is still increasing.^[8,9]^ There is evidence that the mortality rate of ARDS patients is as high as 30% to 40% and is therefore an important cause of death in critically ill patients.^[10–15]^ Despite more than 50 years of research, there is still no specific treatment designated for ARDS, with options limited to supportive care, including protective mechanical ventilation and restriction of fluids,^[16]^ Therefore, finding more effective prevention and treatment strategies for ARDS is an urgent concern.

Traditional Chinese medicine (TCM) characteristically takes a holistic view and differentiates syndromes and treatments, potentially offering advantages and supportive effects in the management of ARDS. There is no record of a disease called ARDS in TCM. However, according to the patients’ clinical symptoms, such as shortness of breath, high fever, dry stools, crimson tongue, and the number of pulse slips, it would be diagnosed as “asthma syndrome.” The syndrome can be subdivided into “asthma syndrome” (early) and “asthma syndrome” (late). The prescriptions determined through syndrome differentiation and treatment has played a role in the diagnosis and treatment of ARDS, laying a foundation for Chinese medicine to participate in its treatment. Chinese medicine has a wide range of mechanisms to treat ARDS, mainly by regulating the cytokine network; protecting endothelial function; through antioxidation; regulating the coagulation/fibrinolysis system, immunity, and water; and through sodium transport.^[17]^

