### Sample size

2.4

Calculating the sample size was based on the effective rate. According to previous research, the effective rate for the treatment group with integrated traditional Chinese and Western medicine is 65.2%, and effective rate for the group with Western medicine alone is 34.8%. The software Power Analysis and Sample Size version 11.0 (PASS 11.0)was used to calculate the sample size of the 2 groups, assuming that 10% of patients are likely to be lost during follow-up, a total of 110 patients will be enrolled.

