### Determination of results

3.2

Since a holistic view of the patient is the core value of TCM, there is no single index that can predict their rehabilitation in order to evaluate the efficacy of JWQYD. Therefore, ARDS needs to be comprehensively evaluated.

1. Efficacy rate: The efficacy rate will be calculated according to the TCM syndrome score (Table 3).^[23]^ The total efficacy rate (%) = (clinical control + significant effect + effective)cases/(total cases × 100%). The score reduction (%) = (points before treatment - points after treatment)/(points before treatment × 100%). The TCM syndrome score will refer to the standard for the diagnosis and curative effect of TCM syndrome issued by the Chinese Society of TCM in 2012.

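### The efficacy rate that sizes the trial has two conflicting grading rules and no grade for a patient who dies before the post-treatment score

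*Protocol article*

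**What the plan says.** All references are to the protocol article.

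- **Role of the outcome.** Section 2.4: "Calculating the sample size was based on the effective rate". The planning rates come from previous research: "the effective rate for the treatment group with integrated traditional Chinese and Western medicine is 65.2" per cent, against 34.8% with Western medicine alone. It continues: "assuming that 10% of patients are likely to be lost during follow-up, a total of 110 patients will be enrolled".
- **Basis of the rate.** Section 3.2, item 1: "The efficacy rate will be calculated according to the TCM syndrome score". The numerator is "clinical control + significant effect + effective)cases" and the denominator is total cases. Score reduction is points before treatment minus points after, divided by points before.
- **Grades.** The list after Table 3 has Cure (reduction above 95%), Significant effect (at least 70%), Effective and Invalid. Cure and Significant effect carry wording on symptoms, signs and laboratory findings. Effective reads "Effective: the clinical symptoms, signs, and laboratory tests are improved. The TCM symptom score is reduced by ≥30" per cent. The lowest grade reads "Invalid: the clinical symptoms and signs are not improved or have worsened. There is a < 30% reduction in the TCM symptom score".
- **Deaths.** No grade mentions death. Section 2.9 lists death among the reasons for stopping and withdrawal, item 6 of section 3.2 records 28-day mortality as a separate outcome, and section 3.7 bases all analyses on intention to treat. The Introduction says "the mortality rate of ARDS patients is as high as 30% to 40" per cent, without a time horizon.

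**The concern.** Responder status turns on the boundary between Effective and Invalid, and two rules are printed for it. Item 1 of section 3.2 points to the score alone. The grade list adds a laboratory condition without naming a test or a size of change. Someone must decide for each discordant patient which rule applies, and that decision moves the rate on which the trial is sized.

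Death is the second problem. The percentage reduction cannot be computed without a post-treatment score. If deaths are left out because they have no score, the comparison is among survivors, which is not the comparison section 3.7 promises. If they are counted as failures, the rates in 2.4 fit only if they were obtained the same way. In a disease with high background mortality this choice can matter, and it should not be open once results are known.

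**Working it through.** **1. Grading rules side by side.** Take scored patients and ask what each rule gives.

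| Score reduction | Laboratory tests | Score alone (3.2, item 1) | Grade list, all conditions required |
|---|---|---|---|
| above 95% | improved | Cure | Cure (symptoms and signs gone or nearly gone) |
| 40% | improved | Effective | Effective (symptoms and signs improved) |
| 40% | not improved | Effective | not Effective (laboratory condition fails); not Invalid (reduction is not below 30%) |
| below 30% | any | Invalid | Invalid if symptoms and signs have not improved |

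Read top down, the score bands alone place every percentage reduction; exactly 95% falls in Significant effect. The conflict arises only from the added conditions, and the third row is where it changes responder status.

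Illustration, with an assumed discordance: if 1 in 10 patients with a reduction of at least 30% lacks laboratory improvement, and the planning rates were graded on score alone, the rates move by up to 0.652 × 0.10 = 6.5 points and 0.348 × 0.10 = 3.5 points, depending on how those patients are graded.

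**2. The planned size.** Inputs from 2.4: p1 = 0.652, p2 = 0.348, 10% loss, 110 in total. Section 3.7 gives a 0.05 threshold. Two-sided testing and 80% power are assumptions, as the article states neither.

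With pooled p = 0.5 and difference 0.304:

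n = [1.960 × √(2 × 0.5 × 0.5) + 0.842 × √(0.652 × 0.348 + 0.348 × 0.652)]² / 0.304² = 41.3 per arm.

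Continuity correction: n/4 × [1 + √(1 + 4/(n × 0.304))]² = 47.6, so 48 per arm and 96 in total. Then 96/0.9 = 106.7, that is 107, or 108 with equal arms. This is close to 110, so the planned size is reproducible on these assumptions.

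**3. Power under a rule for deaths.** Method: exact binomial power of the Pearson chi-square test, two-sided 0.05, 55 per arm, all randomised patients counted. Let m be mortality before the post-treatment assessment, assumed equal in both arms.

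*Case A: the planning rates already count deaths as failures.* The rates stay at 65.2% and 34.8%. Power is 89.3% whatever m is.

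*Case B: the planning rates apply to survivors only.* The rate over all randomised patients is p × (1 − m).

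| m (assumed) | Integrated group | Western medicine alone | Difference | Power |
|---|---|---|---|---|
| 0% | 65.2% | 34.8% | 30.4 points | 89.3% |
| 10% | 58.7% | 31.3% | 27.4 points | 82.3% |
| 20% | 52.2% | 27.8% | 24.3 points | 74.9% |
| 30% | 45.6% | 24.4% | 21.3 points | 66.5% |

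These figures do not also take off the 10% loss. With no deaths and 49 evaluable per arm (55 × 0.9 = 49.5), power is 87.3%.

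**The case against.** The strongest reply is that scored patients can be graded. Section 3.2 says the score is the basis, the bands cover every value, and Table 3 describes the score as one of symptoms and signs. The symptom wording may therefore only describe what each band means, with a fall below 30% as the working meaning of not improved. That stands in part: a reader might infer that the rate cannot be graded at all, and the text does not support that. What remains is the laboratory wording, which the score as described does not cover and which the article does not settle.

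On deaths, total cases together with intention to treat point towards keeping them in the denominator as failures, and an article may leave detail to a fuller document. But this article prints the formula and the grades itself, and the formula needs a value that a patient who has died cannot have.

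Three stronger readings should be resisted:

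- **The summed grade does not exist.** The formula says clinical control where the list says Cure. By position these are almost certainly the same grade, so the mismatch is editorial and has no numerical effect.
- **The 10% loss allowance contradicts the stated mortality.** It is not shown to be wrong. Death is not loss to follow-up; the 30% to 40% is a background figure with no horizon, set beside two weeks of treatment; and section 2.8.2 excludes patients who may die within 12 hours of ICU entry. Deaths counted as Invalid need no loss allowance.
- **The trial is underpowered.** That follows only in Case B, and the article does not say which case holds.

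**Conclusion.** The point holds for the definition of the outcome. The article prints two rules that disagree about a patient with a score reduction of at least 30% and no laboratory improvement, and it gives no grade to a patient who dies before the post-treatment score.

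The effect on power is conditional. It is nil if 65.2% and 34.8% already count deaths as failures. If they describe survivors only, power falls from 89% to about 82%, 75% and 67% at 10%, 20% and 30% mortality before assessment. Those mortality values, equal mortality in the two arms and two-sided testing are assumptions. The article gives no mortality figure for the treatment period.

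**What to change.** In section 3.2, item 1:

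- Grade on percentage reduction in the TCM syndrome score alone, read top down: above 95% Cure, at least 70% Significant effect, at least 30% Effective, below 30% Invalid.
- Report laboratory change as a separate result.
- Count death before the post-treatment assessment as Invalid, with all randomised patients in the denominator.
- Write Cure in the formula in place of clinical control (editorial only).

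In section 2.4, state whether the two planning rates count deaths as failures. If they apply to survivors only, give the power of 110 patients over a range of mortality before assessment, such as 10% to 30%.

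The cost is wording and one recalculated figure. The stated power may become less favourable, and laboratory change no longer contributes to the grade. The changes should be made before unblinding, so that the grading rule cannot depend on the results.

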### Design

2.1

This study is a prospective, multicenter, double-blind, randomized, placebo-controlled clinical trial. The center of research participation includes 4 medical institutions in China: The Affiliated Hospital of Chengdu University of TCM, The Meishan Hospital of TCM, The Neijiang Second People's Hospital, and The ICU of Suining Hospital of TCM.

The trial has been registered in the China Clinical Trial Registration Center (No. ChiCTR1900022693, which was submitted on April 23, 2019, Version.V1.4). After obtaining written informed consent, the 110 participants will be randomly divided into 2 groups at a proportion of 1:1. The 2 groups will be the integrated traditional Chinese and Western medicine treatment group and the Western medicine alone treatment group. The 2 groups of patients will receive 2 weeks of intervention treatment and 1 year of follow-up. The purpose of this experiment is to study the clinical effect of integrated traditional Chinese and Western medicine on patients with ARDS, and to evaluate the efficacy and safety of the JWQYD. At the same time, we will evaluate the long-term effect of adjuvant therapy with Chinese medicine and determine clinically effective treatments for ARDS patients. This study will follow the 2013 Standard Protocol Items: Recommendations for Interventional Trials (SPIRIT). Refer to Figure 1 for information about SPIRIT registration, intervention, and evaluation and Document 1 for the SPIRIT list.^[21]^ The study flow chart is shown in Figure 2.

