### Treatment plan

3.1

Both groups will be treated with Western medicine in accordance with the “Diagnosis and Treatment Guidelines for Acute Lung Injury/Acute Respiratory Distress Syndrome” formulated by the severe medicine branch of the Chinese Medical Association in 2006,^[24]^ which includes active treatment of the primary disease, respiratory support (invasive mechanical ventilation), fluid management, prostaglandin E, sedation and analgesia, and nutritional support.

Western medicine combined with JWQYD: In addition to Western medical treatment, we will administer the decoction of qianyang dan, 25 mL intranasally or orally 4 times a day.

**Western medicine:** Patients in the western medicine treatment group will receive 25 ml of the placebo intranasally or orally, 4 times a day. Index observation should be consistent with the treatment group of integrated traditional Chinese and Western medicine.

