### Statistical analyses

3.7

Before analysis, 2 similar participants with complete data will be carefully examined to ensure that the data is correct. All data analyses will then be based on treatment intention.

The data will be analyzed using the statistical software package SPSS 22.0 (Chicago, IL). The analysis method will be selected according to the distribution characteristics of the data. The measured data will be expressed as the mean ± the standard deviation. First, the normal test and the homogeneity test of variance will be performed. In the case of normal distribution and equal variance, a *t*-test will be performed; otherwise, a nonparametric test will be utilized. The difference will be statistically significant when *P* ≤ .05.

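### Ventilator time (section 3.2, item 4) is defined as a constant or a pre-treatment interval; if a 14-day window is meant, everyone still ventilated at day 14 is tied

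*Protocol article*

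**What the plan says.** Section 3.2 of the protocol article lists seven outcomes. Item 4, length of time with ventilator, is defined in one clause: "the time with the ventilator will be 14 days from the patient participating in the trial to the treatment". Nothing else in the article defines the start, the end or the counting rule for this outcome.

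The related statements are:

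- Section 2.1, on treatment and follow-up: "The 2 groups of patients will receive 2 weeks of intervention treatment and 1 year of follow-up".
- Section 3.2, item 5, on ICU stay: "the actual length of stay = date of leaving the ICU - date of entering the ICU + 1". It has no upper limit.
- Section 3.2, item 6, on 28-day mortality: "the mortality rate from the beginning of the trial to the 28th day will be recorded".
- Section 3.1 names invasive mechanical ventilation among the background treatments for both arms.
- Section 3.7 reports measured data as mean and standard deviation, and uses a t-test if normality and equal variance hold; "otherwise, a nonparametric test will be utilized".

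**The concern.** The clause does not describe a variable that can be analysed. It fixes the value at 14 days, or it describes the time from joining the trial to receiving treatment. A constant cannot differ between arms, and an interval that ends when treatment starts cannot show what the treatment did.

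The sensible repair is to read item 4 as days ventilated during the 14-day course. That reading can be computed, but observation then stops on the last treatment day. A patient weaned on day 15 and one ventilated for 40 days both score 14. Differences in weaning after day 14 disappear from this outcome, and it cannot be lined up with the two neighbouring outcomes, which run to day 28 and to actual ICU discharge.

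At stake is one listed efficacy outcome. Either each analyst has to invent its definition, or the reported difference in mean ventilator days is smaller than the one that occurred.

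**Working it through.** **Readings of item 4.** These are alternatives and cannot all be meant.

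| Reading | Value recorded | Can it show a treatment effect? |
|---|---|---|
| Literal: the time is 14 days | 14 for everyone | No |
| Literal: from participation to treatment | Pre-treatment delay | No |
| Repaired: ventilated days within the 14-day course | min(T, 14) | Yes, with ties at 14 |

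**Is there a figure to reproduce?** No. The article gives no ventilation durations, no expected difference and no share expected to be ventilated beyond day 14. Its sample size of 110 rests on effective rates (section 2.4). What follows illustrates the repaired reading only.

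**Inputs**
- From the article: 110 patients at 1:1, so 55 per arm; limits at day 14 (treatment) and day 28 (mortality); significance at P ≤ .05, taken as two-sided.
- Assumed: exponential ventilation time T; control median m of 5, 7, 10 or 14 days; treated mean 0.7 times the control mean; no deaths; no drop-out.

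**Formulas**
- Control mean μ = m / ln 2; treated mean 0.7μ.
- Share tied at limit c: exp(−c/μ).
- Mean of the limited time: μ(1 − exp(−c/μ)).

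**Worked case, m = 10**
- μ = 10/0.6931 = 14.43; treated mean 0.7 × 14.43 = 10.10.
- Tied at 14: controls exp(−14/14.43) = 0.379; treated exp(−14/10.10) = 0.250.
- Day-14 limit: 14.43 × 0.621 = 8.96 and 10.10 × 0.750 = 7.57; difference 1.39 days.
- Day-28 limit: 14.43 × 0.856 = 12.36 and 10.10 × 0.9375 = 9.47; difference 2.89 days.

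**All cases.** Power is from 20,000 simulated trials of 55 per arm with the Mann-Whitney test.

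| Control median (days) | Controls tied at 14 | Mean difference, day-14 limit | Mean difference, day-28 limit | Rank power, day 14 | Rank power, day 28 |
|---|---|---|---|---|---|
| 5 | 14% | 1.44 | 2.04 | 36% | 36% |
| 7 | 25% | 1.48 | 2.53 | 33% | 35% |
| 10 | 38% | 1.39 | 2.89 | 31% | 35% |
| 14 | 50% | 1.21 | 2.96 | 28% | 34% |

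The day-14 limit keeps 71% of the day-28 mean difference at the shortest median (1.44/2.04) and 41% at the longest (1.21/2.96).

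**Why the rank test.** An exponential time is skewed and its standard deviation equals its mean, so the treated variance is 0.7² = 0.49 of the control variance. Both conditions that section 3.7 sets for a t-test fail. A t-test would show a larger loss (35% against 43% at m = 7; 25% against 36% at m = 14), but it is not the test that section 3.7 would select for such data.

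**Deaths.** The introduction cites ARDS mortality of 30% to 40%. Take 35% by day 28 at a constant rate, independent of ventilation. Survival to day 14 is then √0.65 = 0.806, and the tied control shares become 12%, 20%, 31% and 40%.

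**Another shape.** With lognormal times (control median 5 to 18 days, log-SD 0.8 to 1.0, ratio of medians 0.7, no deaths), 10% to 62% of controls are tied. The day-14 limit keeps between 76% (1.55 of 2.04 days) and 14% (1.25 of 8.97 days) of the unlimited mean difference. The day-28 limit keeps between 94% (1.92 of 2.04) and 35% (3.11 of 8.97). With log-SD 0.8, rank power at day 14 against day 28 is 0.633 against 0.634 at median 5, and 0.522 against 0.609 at median 18.

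**The case against.** The best defence is that item 4 is a translation slip and that a 14-day window is a reasonable choice. It matches the treatment course, and nothing obliges every outcome to share the mortality horizon. Later benefit is not wholly unseen, since ICU stay is unlimited and deaths are recorded to day 28. This stands in part: a clearly stated 14-day window would be a weaker choice but not an error. It does not rescue the present clause, which states no usable window. Treatment length also need not set the observation period, and the Discussion itself lists doubt about the 14-day treatment length as a limitation.

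A reader might go further and infer that the outcome misses much of the ventilation course, or that the window would make the trial report no effect on ventilation when there is one. The documents do not support this. They give no durations, and with a short median few patients reach the limit. Under the rank test the power loss is small. Power in the exponential illustration is only about a third even with a day-28 limit, so a null result there would owe more to the sample size than to the window.

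The shrinkage of the mean difference does survive the defence, because section 3.7 commits to reporting means and standard deviations.

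**Conclusion.** The definition is wrong as written and has to be replaced. That conclusion needs no assumption.

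The cost of a 14-day window, if that is what is meant, is conditional. Under the exponential illustration it ties 14% to 50% of controls (12% to 40% with 35% mortality). It records a mean difference of 1.2 to 1.5 days where a day-28 limit records 2.0 to 3.0, and it lowers rank-test power by about 0 to 7 points. All of this depends on assumed durations and an assumed 30% shorter treated mean.

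The consequence is confined to one of seven outcomes, and the sample size rests on the effective rate, so the primary conclusion is untouched. How to score patients who die on the ventilator is a separate issue.

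**What to change.** Replace item 4 with: number of days on the ventilator from randomisation to day 28. If the treatment-period count is of interest, keep days ventilated to day 14 as a supportive figure under its own label.

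The change is one line in the outcome definition. Day 28 is already a trial horizon, and ventilator dates for patients still in the ICU stand in the ICU chart. The cost is two more weeks of chart abstraction for patients still ventilated after day 14. A day-28 limit still ties some patients (2% to 25% of controls in the exponential illustration, from exp(−28/μ)), but far fewer than a day-14 limit.

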### Randomization and assignment blinding

2.5

Members of The Sichuan TCM Evidence-Based Medicine Center will use SAS 9.2 software (SAS, Cary, NC) to generate 110 random serial numbers. After screening and baseline evaluation, the patients with ARDS will be randomly divided into 1 of the 2 groups. Eligible patients will be assigned to the integrated traditional Chinese and Western medicine treatment group or the Western medicine alone treatment group at a proportion of 1:1. The group number will be provided in a carbon-free sealed envelope. The envelope will be kept by the study administrator, who will not be directly involved in any participant's recruitment or follow-up, and the group number will be disclosed later. The administrator will open an envelope and provide participants with their group number on the day of inclusion.

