#### Exclusion criteria

2.8.2

Patients who meet 1 or more of the following exclusion criteria cannot be included:

(1)Pregnant or lactating women(2)Those who are allergic to the drugs used in the program(3)Those with surgical pointer(4)Patients with serious bodily diseases, acquired immune deficiency syndrome, or malignant tumors(5)Patients who may die, refuse active rescue, or are unwilling to receive Western medical treatment within 12 hours after entering the ICU(6)Currently participating in other drug research studies(7)Patients with severe diseases of the liver, kidney, hemopoietic system, or metabolic endocrine system, leading to organ dysfunction.

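### ICU length of stay is counted from ICU entry rather than from randomisation, so it includes days that treatment cannot affect; this adds noise, not bias, and is cheap to correct

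*Protocol article*

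**What the plan says.** Item 5 of section 3.2 (Determination of results) fixes ICU length of stay by formula: "the actual length of stay = date of leaving the ICU - date of entering the ICU + 1". The clock starts on the date of ICU entry.

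Randomisation is a later event. Section 2.5 says: "After screening and baseline evaluation, the patients with ARDS will be randomly divided into 1 of the 2 groups". It adds: "The administrator will open an envelope and provide participants with their group number on the day of inclusion". Before that, a patient must meet the ARDS definition, have the TCM syndrome judged by two physicians (section 2.7) and have consent signed (section 2.8.1).

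The eligibility lists in section 2.8 set no limit on ICU time already spent. The one reference to time since ICU entry, "within 12 hours after entering the ICU", belongs to an exclusion for expected death or refusal of care. It is not a limit on the time to randomisation.

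Two neighbouring outcomes start the clock elsewhere. For 28-day mortality, "the mortality rate from the beginning of the trial to the 28th day will be recorded". For ventilation, "the time with the ventilator will be 14 days from the patient participating in the trial to the treatment"; the sentence is hard to parse, but its reference point is entry into the trial.

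For measured data, section 3.7 names a t-test if normality and equal variance hold; "otherwise, a nonparametric test will be utilized". It names no adjustment for ICU days before randomisation.

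**The concern.** An outcome in a randomised comparison should measure what can happen after allocation. Item 5 instead adds together two periods: ICU days before randomisation, which are fixed before any study drug is given, and ICU days after it, which treatment might change. Only the second carries information about JWQYD.

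Two hypothetical patients with the same course after randomisation show the effect. One enters the ICU on day 1, is randomised on day 8 and leaves on day 18, scoring 18 − 1 + 1 = 18 days. The other enters and is randomised on day 1 and leaves on day 11, scoring 11 − 1 + 1 = 11 days. The 7-day gap has nothing to do with treatment.

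Such variation is possible because the Introduction's list of causes ("ARDS can be attributed to a variety of factors, including sepsis, multiple injuries, massive blood transfusions, pneumonia, aspiration, and lung contusions, among others") includes some that can arise during an ICU stay. At stake is the precision of the ICU-stay comparison, and whether this outcome shares a starting point with the others listed beside it.

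**Working it through.** **1. The plan's own figure.** The article gives no mean, SD or target difference for ICU stay. Its only sample-size figure is N = 110, based on effective rates of 65.2% and 34.8% with 10% loss (section 2.4). Power, sidedness and test are not stated. Assuming 80% power, two-sided 5% and a continuity-corrected comparison of two proportions, the requirement is 48 per arm. Then 48 / 0.90 = 53.3, rounded up to 54 per arm, or 108 in total, within two patients of 110. ICU stay plays no part in this, so changing item 5 leaves N as it is.

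**2. Expected difference between arms.** Write total stay as T = P + D, with P the ICU days before randomisation and D those after. P is fixed before allocation, so E(P) is the same in both arms, and the expected difference in T equals the expected difference in D. A simulation of 20,000 trials with 55 per arm agrees. It assumed D in controls with mean 15 and SD 10, and P with mean 0.5 to 4 days. The mean difference was −5.37 days with either starting point and type I error was 4.9% to 5.0%. Power fell from 92.9% to 86.4% when P averaged 4 days.

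**3. Loss of precision.** With s the SD of D, p the SD of P and ρ their correlation, SD(T) = √(s² + p² + 2ρsp). Power ≈ Φ(δ / [SD(T) × √(2/55)] − 1.96), where √(2/55) = 0.1907.

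Assumed: s = 8 days, δ = 4.35 days, ρ = 0. None of these comes from the article.

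| p (days) | SD(T) | Standard error | δ / SE | Power | Information kept, 64/(64 + p²) |
|---|---|---|---|---|---|
| 0 | 8.00 | 1.53 | 2.85 | 81% | 100% |
| 2 | 8.25 | 1.57 | 2.77 | 79% | 94% |
| 4 | 8.94 | 1.71 | 2.55 | 72% | 80% |
| 6 | 10.00 | 1.91 | 2.28 | 63% | 64% |

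**4. Sensitivity to the assumptions.** Here δ is chosen to give 80.0% power when days are counted from randomisation, again with 55 per arm.

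| s, δ (days) | ρ | p = 1 | p = 2 | p = 3 | p = 5 |
|---|---|---|---|---|---|
| 10, 5.34 | 0 | 79.6% | 78.4% | 76.5% | 70.7% |
| 10, 5.34 | 0.3 | 77.3% | 73.9% | 70.1% | 61.4% |
| 6, 3.21 | 0 | 78.9% | 75.7% | 70.7% | 57.6% |
| 6, 3.21 | 0.3 | 75.1% | 68.7% | 61.4% | 47.3% |

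With p = 1 and no correlation the loss is about one percentage point or less. It becomes material when P varies by several days, and is larger if patients with long earlier stays also stay longer afterwards.

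**5. Chance imbalance.** The standard error of the difference in mean P between arms is p × 0.1907: 0.38, 0.76 and 1.14 days for p = 2, 4 and 6. A 1-day imbalance would move the estimate by 1 day. At p = 2 that is 1 / 0.38 = 2.6 standard errors, so it is unlikely; at p = 4 or 6 it is unremarkable.

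**The case against.** A reader might infer that the definition shifts the comparison between arms. The article does not support this. Earlier ICU days are settled before a 1:1 allocation, so they cancel in expectation. Any chance imbalance is already reflected in the standard error, as for any other baseline variable. This part of the objection stands in full.

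The size can also be challenged. The article documents no long stays before randomisation. Its causes of ARDS include pneumonia, multiple injuries and lung contusion, which may equally be the reason for ICU admission, and the 12-hour wording fits early screening. Tables 1 and 2 and the enrolment schedule in Figure 1 are not available to read, so a timing condition there can be neither asserted nor ruled out. The SDs and the 4.35-day difference are assumptions. The power formula compares means, whereas a nonparametric test may well be used for ICU stay. All of this stands: the loss may be negligible.

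Finally, entry to exit is literally ICU length of stay, the formula is explicit and reproducible, and an analysis plan could add adjustment. These points limit the weight. They do not remove the fact that the stated rule includes time treatment cannot affect, while two outcomes beside it start at the trial.

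**Conclusion.** The point holds as a matter of precision. Item 5 starts the clock before randomisation, out of step with 28-day mortality and ventilator time, and the text available neither limits the earlier interval nor adjusts for it. The consequence is added variance, with no systematic bias and no inflation of type I error.

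The loss is negligible if patients are randomised within about a day of ICU entry and material only if that interval varies by several days. The article does not show which applies, so the fall from 81% to between 79% and 63% is illustrative only. ICU stay is one of seven listed outcomes and does not drive the sample size. This is a minor improvement, worth making because it costs almost nothing.

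**What to change.** Redefine item 5 as ICU days from the date of randomisation to the date of leaving the ICU, applying the same plus-one convention in both arms. Total ICU stay can still be reported descriptively.

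Alternatively, keep the formula and adjust the comparison for ICU days before randomisation. In a linear model with that covariate, the residual SD of T is s√(1 − ρ²), the same as if D had been analysed with the same covariate, so the added noise is removed. This needs a regression model in place of the simple test in section 3.7.

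It would help to state the starting point of every timed outcome at the same time.

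The cost is one line in the outcome definition, or one covariate in the analysis. The existing formula already needs the ICU entry and exit dates, and the inclusion day is known because the envelope is opened then, so no new data are required. The downside is small: ICU days from randomisation are less directly comparable with reports of total ICU stay. N = 110 does not change.
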